### 3) Multiple ascending dose study (60mg, 120 mg, 240 mg, 480 mg, 120 mg(elderly))

[figure not shown]

Volunteers for this study are selected as subjects if they are judged eligible for this study by undergoing screening procedures such as history taking, physical examinations, and clinical laboratory tests within 4 weeks (-28 ~ -2d) before the first administration.

Subjects are randomized after admission to the Clinical Trials Center, Seoul National University Hospital in the afternoon of the day of admission (-1d), and have dinner around 6 PM. On the dosing day (1d), the investigational drug is orally administered with 150mL of water at around 9 AM (reference time, 1d 0h), and food including drinking water is prohibited from 1 hour before administration to 4 hours after administration. (For the elderly, drinking water is prohibited for up to 2 hours and food intake is prohibited for up to 4 hours after administration.) Thereafter, the subjects conduct the study according to the predefined schedule and the administration of the investigational drug is continued in the hospitalized state for the repeated administration period (7 days). Subjects should maintain a fasting state for at least 10 hours before administration, and food including drinking water is prohibited from 1hour before administration. On 1d and 7d, drinking water and meals are prohibited until 4 hours after the end of administration (For the elderly, drinking water is prohibited for up to 2 hours and food intake is prohibited for up to 4 hours after administration.), and on the other administration days except for 1d and 7d, food including drinking water is prohibited until 2 hours after the end of administration. On 2d, 3d, 4d, 5d, and 6d, pharmacokinetic blood sampling is performed before administration to confirm that steady state is reached. On the morning of 7d, after oral administration of the investigational drug once, examination and evaluation are performed according to the planned schedule and then discharged on 10d. After discharge, subjects visit the Clinical Trials Center on the morning of 11d, 12d, and 13d to perform the scheduled procedures.

The subjects who complete whole study conduct the Post Study Visit(PSV) between 18d and 22d at their convenience.

## 10.2. Blinding and Unblinding Procedures

### 10.2.1. Blinding

The label indicated in the protocol is for the study drug and placebo provided only to pharmacies, and neither the principal investigator nor the subject cannot know the type of drug being administered before the end of the study. Clinical investigational drugs are monitored by a separate monitoring agent not involved in this clinical trial, and the monitoring agent and the managing pharmacist are excluded from blinding. The investigational drug manager must confirm that the appearance of the investigational drug is the same between the test drug and the placebo, that is, the test drug and the placebo are indistinguishable from each other before assignment of the investigational drug and code breaking. This clinical study is a dose blocked-randomized, double-blind, placebo-controlled, single and multiple dosing, dose-escalation phase I clinical trial and is conducted in a double-blind manner to exclude subjective judgments of subjects and investigators.

In order to maintain the double-blindness, a placebo with the same formulation and appearance that cannot be distinguished from the KDS2010 tablet will be used, and the packaging will be the same. By maintaining double-blindness for the investigator and the subject, make sure that the investigator or subject avoids bias in evaluating treatment effects and adverse events.

The person in charge of randomization generates a randomization code according to the randomization method and provides the randomization code to the laboratory management pharmacist. Accordingly, the managing pharmacist dispenses the investigational drug (test drug or placebo) assigned to each subject number. For each subject, the drug for clinical trial is determined according to their own randomization number, and the randomization code is not disclosed unless the randomization code is released after the clinical trial for each stage is completed. However, in case the blinding is removed due to the occurrence of an emergency such as a serious adverse reaction, the person in charge of randomization should make a blinding envelope with the randomization number and deliver it to the principal investigator and keep it. In addition, the blindfold bag must be properly stored until the end of the clinical trial by the principal investigator and can only be opened according to the established procedure.

### 10.2.2. Unblinding Procedures

If it is determined that the blinding should be removed due to the occurrence of an emergency that threatens the safety of the subject, the investigator must immediately notify Neurobiogen Co., Ltd. or the monitor of the contract research organization delegated by Neuro Biogen Co., Ltd. The monitor has an obligation to immediately contact the person in charge of Neurobiogen. After obtaining the relevant information, the person in charge of NeuroBiogen determines whether or not to remove the blinding in consultation with the investigator and leaves a document on the decision. In case that immediate contact with the sponsor Neurobiogen is not possible, the investigator must proceed with unblinding and inform Neurobiogen Co., Ltd. or the monitor of the contract research organization delegated by Neurobiogen Co., Ltd. as soon as possible of the breaking of the double blinding. And the reason for unblinding without consulting with the sponsor should be documented. If the investigator becomes aware of the subject identification code during the study period, the investigator should endeavor to exclude bias in the evaluation of safety.

After the clinical study is over, all data is resolved through the 'Query'. When the database is confirmed to be complete and correct, the data will be locked and the randomization code information will be released. Subsequent changes to the database are possible only with the written consent of the sponsor and the database administrator.

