The randomization number is used as the subject identification code during the clinical study period. After generating the randomization list, the person in charge of randomization sends it to the clinical trial pharmacist. The clinical trial pharmacist dispenses investigational drugs for each subject according to the randomization list.

Until the end of this clinical study, all investigators, subjects, and those who conduct clinical study, except for the clinical trial pharmacist, must remain blinded. And if it is necessary to unblind during the clinical study, proceed according to the procedure mentioned in 10.2.2 of this clinical study protocol.

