#### 10.5. Dose Escalation to the Next Dose Level

When safety data up to the the last pharmacokinetic sampling day of the all subjects for each dose group are available, the next dose level can proceed if it is determined that safety and tolerability have been adequately demonstrated through the review of the internal safety review committee (SRC) composed of the Investigators and the Sponsor. The elderly dose group(120 mg) of the multiple dose study proceeds after the maximum tolerated dose (MTD) group or the 480 mg dose group is completed. When proceeding from a single dose study to a multiple dose study, and when determining the administration dose in the elderly dose group within the multiple dose study, the appropriate administration dose is determined after review by the Safety Review Committee (SRC) including independent experts. The SRC is made up of the investigators, the sponsor, and cardiovascular or neurological experts.

When determining whether safety and tolerability have been adequately demonstrated, the Principal Investigator remains blind to the treatment group (test group or placebo group). However, when the treatment information is critical to the subject safety and/or dose escalation decision, the Principal Investigator could be unblinded.

Considering the drug's half-life after administration and study schedule in the single and multiple ascending dose study, safety and tolerability is evaluated within the last pharmacokinetic sampling day of all subjects in the dose group. If it is judged acceptable through the internal SRC review, proceed to the next dose level after discussion and the investigator's judgment has priority for adverse events occurring within the period.

After evaluating the severity of adverse events(safety test results(including clinical laboratory tests, vital signs, etc.) and adverse reactions of all subjects who administered the investigational drug) based on the Common

Terminology Criteria for Adverse Events (CTCAE) version 5.0 or the latest version, the Principal Investigator can decide whether or not to discontinue the entire study. In addition, if the following occurs, the dose escalation can be stopped through discussion between the investigator and the sponsor.

- When a Grade 3 or higher adverse drug reaction occurs in more than 1/4 of the subjects
- When a Grade 4 or higher adverse drug reaction occurs in one or more subjects

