**11. Criteria for Suspension and Early Termination of Clinical Study****11.1. Suspension of Clinical Study**

If the Principal Investigator decides that it is not wise to continue the clinical study in light of the results observed during the clinical study, part or all of the study may be discontinued in consultation with the sponsor.

- 1) The principal investigator may suspend part or all of the clinical study without consultation with the sponsor if there is a serious reason that the subject cannot continue the clinical study and it is judged that it is urgent.
- 2) The sponsor may suspend part or all of the clinical study for safety or management reasons.
- 3) If the clinical study is early terminated or suspended, the principal investigator must immediately notify the subject of this fact and ensure that appropriate measures and follow-up can be made.
- 4) The eCRF and clinical study progress status and results for the subject who have progressed until the time of suspension are organized and delivered to the sponsor, and all study-related data (complete, incomplete or undescribed eCRF and investigational drug, etc.) must be returned to the sponsor.
- 5) If the clinical study is suspended, it must be reported to the IRB and the Ministry of Food and Drug Safety.

If the principal investigator determines that unexpected problems, serious protocol violations, or serious adverse events occurring in the course of the clinical study are not enough to qualify for the suspension of the clinical study, the clinical study will be continued in accordance with the results of consultation with the sponsor and the IRB's review. If necessary, the clinical study can proceed by amending the clinical study protocol.

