
### **17.4. Actions to Secure Subject Safety**

The investigator should thoroughly confirm that the subjects are healthy enough to participate in clinical trials by checking the health status of each subject before enrollment. In addition, the investigator will fully understand

protocol and investigational drugs, and conduct clinical study according to the protocol. Investigators must be best to ensure the safety of the subject. If an adverse event occurs that requires treatment, the subject should be given a diagnosis and appropriate treatment by a medical doctor. In addition, if necessary, observation should be made until the relevant adverse event disappears or follow-up becomes impossible. During the clinical study period, if a subject wants to receive treatment due to an adverse event, or if the investigator determines that medical treatment is necessary, he/she must immediately visit the clinical trial institution and undergo relevant examinations. If the investigator evaluates the adverse event and test results and determines that the study should be stopped, or if the subject wants to stop the study, the investigator will promptly proceed with the procedure following the end of the clinical study and actively provide treatment to the subject to alleviate the symptoms.

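### Protocol section 10.2.2 leaves emergency unblinding to the sponsor once it is reached, sets no time limit, and does not let the investigator proceed if the sponsor is slow or disagrees

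*Protocol*

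**What the plan says.** Protocol section 10.2.2 covers an emergency that threatens the safety of a subject. The investigator must notify the sponsor, or the monitor of the contract research organization, at once, and a monitor who is notified must contact the sponsor at once. When the sponsor has the relevant information, "the person in charge of NeuroBiogen determines whether or not to remove the blinding in consultation with the investigator", and the decision is documented. There is one exception: "In case that immediate contact with the sponsor Neurobiogen is not possible, the investigator must proceed with unblinding". The investigator must then inform the sponsor or monitor as soon as possible and document why the sponsor was not consulted.

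The means to unblind are on site. Under section 10.2.1 the person in charge of randomization "should make a blinding envelope with the randomization number and deliver it to the principal investigator", but the same section says that it "can only be opened according to the established procedure". Section 10.3.2 adds: "if it is necessary to unblind during the clinical study, proceed according to the procedure mentioned in 10.2.2".

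**The concern.** The physician at the bedside usually has the best view of whether knowing the allocation would change the care of a subject in danger. Section 10.2.2 places the decision elsewhere once contact is made. The steps up to contact are marked as immediate, but gathering the information and deciding are not. The exception turns on failure of contact and not on failure to obtain a timely answer.

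At stake is the part of emergency care that depends on knowing whether the subject took active drug. If the sponsor is reached and then takes time, or prefers to keep the blind, the text gives the investigator no route to the envelope.

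**Working it through.** No stated figure needs reproducing for the main point, which is a reading of the text. The sections that bear on unblinding are set side by side below.

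| Protocol section | What it provides | Does it let the investigator open the envelope if the sponsor is reached but is slow or disagrees? |
|---|---|---|
| 10.2.2, main rule | The sponsor's person in charge decides and the investigator is consulted | No |
| 10.2.2, exception | The investigator must unblind when immediate contact is not possible | No; contact has been made |
| 10.2.1 | The principal investigator keeps the envelope and opens it only under the procedure | No; it depends on 10.2.2 |
| 10.3.2 | Refers unblinding during the study to 10.2.2 | No; it leads back to the same rule |
| 10.5 (repeated in the synopsis) | "when the treatment information is critical to the subject safety and/or dose escalation decision, the Principal Investigator could be unblinded" | Not stated; it belongs to the escalation review and names no decision-maker |
| 11.1 | "The principal investigator may suspend part or all of the clinical study without consultation with the sponsor", where the reason is serious and the matter urgent | No; it covers suspension, not the code |

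The situations under 10.2.2 then divide as follows.

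1. The sponsor cannot be reached immediately: the investigator must unblind. Covered.
2. The monitor is reached but the relay to the sponsor stalls: immediate contact with the sponsor has failed, so the exception reasonably applies. Covered.
3. The sponsor is reached and agrees promptly: the code is opened. Covered.
4. The sponsor is reached and then delays or disagrees: neither a time limit nor a right to proceed is given. Not covered.

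Only situation 4 is exposed.

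**Cost of the remedy to the blind.** Inputs, from section 9.1: a cohort of 8 with 6 on active drug and 2 on placebo. Assumptions: no replacement subjects, one envelope per randomization number, and no other information on allocation.

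- Before any code is opened: P(active) = 6/8 = 75.0%; possible allocations C(8,2) = 28.
- One active code opened: for each of the other 7, P(active) = 5/7 = 71.4%; possible allocations C(7,2) = 21.
- One placebo code opened: for each of the other 7, P(active) = 6/7 = 85.7%; possible allocations C(7,1) = 7.

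No other subject's allocation becomes certain after one opened code. These figures measure the cost of the remedy. They say nothing about how likely or how large the harm is.

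**The case against.** The strongest reply is that 10.2.2 never addresses disagreement. It states no rule of refusal, it requires consultation, and its opening condition, that a need to unblind has been determined, may well describe the investigator's own judgement. On that view the section is unclear about who prevails, and a reader who infers an express sponsor veto goes beyond the text. This stands in part: no veto is written. But the party who decides is named, and it is the sponsor. The only stated departure is failed contact, so a plain reading does not let the investigator proceed.

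A second reply is that care does not wait on the code. This stands. Section 17.4 provides: "If an adverse event occurs that requires treatment, the subject should be given a diagnosis and appropriate treatment by a medical doctor". Section 9.3 lets the investigator withdraw a subject, and section 11.1 permits urgent suspension by the principal investigator alone. A reader might infer that the sponsor can hold up treatment, and the protocol does not support that.

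A third reply concerns the contrast between 11.1 and 10.2.2. It is tempting to call it a contradiction that the principal investigator may stop the whole study alone but may not open one envelope. Suspension and code-breaking are different acts, so different consultation rules can coexist. The contrast also shows that the urgent protective step is already in the investigator's hands.

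Finally, section 10.5 shows that the protocol does not rank blinding above subject safety. That is fair, but with no decision-maker named it does not close the gap.

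**Conclusion.** The point holds as a minor safety matter. Once the sponsor is reached, 10.2.2 gives it the emergency unblinding decision without a time limit, and no other section of the protocol lets the investigator proceed if the sponsor is slow or disagrees.

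The size is small and cannot be expressed as a rate. The rule applies to every cohort, but it matters only when a safety-threatening emergency arises, the investigator wants the code, and a sponsor reached promptly then stalls or disagrees. The planned sample size and the 6:2 allocation ratio might be read as measures of exposure. They are not: they give neither the frequency of such events nor the probability of active drug in a subject whose emergency looks drug-related. The protocol names no rescue treatment that depends on allocation, and no endpoint, analysis population or escalation rule is affected.

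The conclusion rests on taking the named decider in 10.2.2 at face value and on the envelopes being individual, as 10.2.1 suggests.

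**What to change.** In Protocol section 10.2.2, state that in an emergency threatening a subject's safety the investigator makes the final decision to open that subject's envelope. The investigator consults the sponsor first only if this causes no delay, and notifies the sponsor or the monitor immediately afterwards with the reason documented. Sections 10.2.1 and 10.3.2 already defer to the procedure and need no change.

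The cost is one or two sentences, with no new materials because the envelopes are already with the principal investigator. The downside is that codes may be broken slightly more often. Each extra opened code gives the principal investigator, who is meant to stay blind for the escalation review in 10.5, the partial information on the rest of the cohort worked out above. That is a modest price.

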## 10.3. Assignment of Subject Identification Number

### 10.3.1. Screening Number

Screening numbers are assigned to the subjects who provided a written consent to participate in the clinical study in the order of the informed consent form signed. The screening numbers start with S001 and will be given in regular sequence.

### 10.3.2. Randomization Number

On the day of admission (-1d), the randomization numbers are assigned in the order of passing the screening tests finally (If the subjects pass the screening tests on the same day, subject numbers will be assigned in the order of randomization numbers). They are randomly assigned to the test group or Control group according to the randomization number.

The randomization number consists of five digits (RXXXX) and has a certain rule of one letter (R) and four digits. The first number represents each single/multiple dose study (1: single ascending dose study; 2: multiple ascending dose study). The second number represents the cohort. The third digit indicates whether the subject is a replacement subject or not (0: existing subject; 1: first replacement subject). The last single digit represents the order of participating subjects. The randomization number assigned to each subject is used as a subject identification code to recognize the subject until the end of the clinical study. Subjects who withdraw consent or have the study discontinued for any reason retain their subject number regardless of the administration of investigational drugs.

| Single ascending dose study |                      | Multiple ascending dose study |                      |
|-----------------------------|----------------------|-------------------------------|----------------------|
| Cohort                      | Randomization number | Cohort                        | Randomization number |
| 1                           | R1101 ~              | 1                             | R2101 ~              |
| 2                           | R1201 ~              | 2                             | R2201 ~              |
| 3                           | R1301 ~              | 3                             | R2301 ~              |
| 4                           | R1401 ~              | 4                             | R2401 ~              |
| 5                           | R1501 ~              | 5                             | R2501 ~              |
| 6                           | R1601 ~              |                               |                      |

The randomization number is used as the subject identification code during the clinical study period. After generating the randomization list, the person in charge of randomization sends it to the clinical trial pharmacist. The clinical trial pharmacist dispenses investigational drugs for each subject according to the randomization list.

Until the end of this clinical study, all investigators, subjects, and those who conduct clinical study, except for the clinical trial pharmacist, must remain blinded. And if it is necessary to unblind during the clinical study, proceed according to the procedure mentioned in 10.2.2 of this clinical study protocol.

#### 10.4. Administration of Investigational Drugs

##### 10.4.1. Administration methods

After fasting for at least 10 hours, subjects should orally administer the investigational drug together with 150 mL of water on an empty stomach around 9:00 am on the day of administration of the investigational drug. (However, in the case of the food effect study among single ascending dose study, both the administration in the fasting state (phase 1) and the administration (phase 2) after a high-fat meal (900 Kcal or more, fat content 35% or more) are carried out.)

Subjects should swallow the investigational drug whole with 150 mL of water, and should not chew the drug before swallowing. Subjects should fast for 4 hours after administration, and should sit at 45 degrees or more or stand upright until 2 hours after administration.

